### Study setting, data source, and study population

A major step toward raising and improving the standard of care in oncological health services in Germany was the nationwide implementation of clinical cancer registries, enacted by the Cancer Early Detection and Registry Act (Krebsfrüherkennungs- und -registergesetz, KFRG) in April 2013 (Federal Ministry of Health of Germany 2013). This emulated target trial study will use data from the Mecklenburg-Western Pomerania Cancer Registry, a registry providing ≥ 90% completeness of coverage (Arndt et al. 2020).

The estimated population of Mecklenburg-Western Pomerania was 1,629,464 inhabitants as of December 31, 2023 (Statistical Office of Mecklenburg-Western Pomerania 2024). The federal state covers 23,294 square kilometers and is the least densely populated state in Germany, with only 70 people per square kilometer (Statistical Office of Mecklenburg-Western Pomerania 2024). There are currently 38 hospitals in the whole region, just five of which function as certified colorectal cancer treatment centers, Federal Statistical Office of Germany 2024; OncoMap 2024). Compared to all German federal states, Mecklenburg-Western Pomerania had the sixth highest age-standardized incidence rate (ASIR) of colorectal cancer in men and the fourteenth highest in women in the period 2019–2020 (Robert Koch Institute 2024). Between 2008 and 2022, the ASIR of colon cancer in the region was 33.6 per 100,000 population for men and 21.1 per 100,000 population for women 35 (Interactive report of Mecklenburg-Western Pomerania Cancer Registry 2024). Our study population consists of all adult patients with a confirmed diagnosis of primary stages I–III colon cancer between January 1, 2008 and December 31, 2018, who underwent major elective laparoscopic or open surgery (OPS codes 5–455, 5–456, 5–457, and 5–458) during this period (ICD-10-GM 2023). Figure1 below shows the present locations of the Registry’s catchment areas, detailed by the postcode area.

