Follow-up	Follow up begins at diagnosis and the random allocation of patients to either treatment arms and then scheduled follow-up information according to German S3- guideline for colorectal cancer (German Guideline Program in Oncology 2019).	Patients will be followed from time-zero (date of diagnosis) until death from any cause, last date of information or administrative censor date (31.12.2023), whichever will come first.
Censoring	Loss to follow-up, administrative censor date (31.12.2023).	Same as target trial
Causal contrast	Intention-to-treat effect, per-protocol	Observational analogue of the per-protocol effect
Effect measure	Hazard ratio (HR), mean survival time difference	Same as target trial
Analysis plan	Multivariable Cox regression, absolute risk difference and restricted mean survival time (RMST)	Inverse-probability weighted Royston- Parmar parametric survival model. Further to the HR, absolute risk-difference, RMST difference will be calculated.
Covariate adjustments	ϖ Socio-economic characteristics: Age at colon cancer diagnosis (in years) and sex. ϖ Clinical characteristics: UICC^b^ stage (I, II or III), treating institutions, tumor laterality (left or right), treatment period (2008–2009, 2010–2014, 2015–2018), performance score (ECOG = 0, 1, or 2), hospital classification (certified colon center or not), local residual tumor margin status (yes, no, or not assessable), grade (low, intermediate or high), and number of harvested lymph nodes (< 21 or ≥ 21).	ϖ Socio-economic characteristics: same as target trial. ϖ Clinical characteristics: same as target trial.
Sensitivity analysis	Excluding cases with missing values (complete case analysis, CCA)	Sensitivity analyses: - 1) Repeat the same analysis on patients with complete case data - 2) Including all advanced local disease (stage T4N0-2M0) cases - 3) Quantitative bias analysis using the E-value method to evaluate the effect of potential residual confounders (BMI, comorbidity, previous abdominal surgery for non-malignant indications)
Comparator analysis		Comparator analyses: - Comparator 1) DAGs-guided naïve analysis of using fully adjusted cox proportional hazards model - Comparator 2) An Inverse-probability-weighted regression-adjustment (Doubly robust) analysis

^a^ ICD-10 = The International Classification of Diseases, 10th Revision

^b^ UICC = Union for International Cancer Control

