Patients will be followed up from the date of assignment to either treatment modality until death from any cause (the outcome of interest), the last date of follow-up, or the administrative censor date (31.12.2023), whichever occurs first. This administrative censor date is chosen to ensure that patients are observed for at least five years. Patient follow-up will be made in accordance with the recommendation of the German S3- guideline for colorectal cancer (German 2019). In the emulated study, we will start following the patients at time-zero, which is defined as the time point at which the eligibility criteria will be met. The initiation of treatment will have to occur within the first three months after the diagnosis of colon cancer (defined grace-period). Follow-up will end on the date of death, last date of follow-up, or 60 months after time-zero, or the administrative censor date Dec. 31, 2023, whichever will occur first. The main outcome will be 5-year OS, which refers to the duration from time-zero until death from any cause. The estimated hazard ratio will be complemented by the mean survival difference (at 1, 3, and 5 years) between the patients treated with laparoscopic and open surgery, respectively. Since our study covers a long period of time (2008 to 2018), treatment period-specific analyses will be performed to mitigate potential bias that may be induced by changes in clinical knowledge and practice over time (Hou et al. 2022).

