In the web-based DAGitty environment (https://www.dagitty.net/), we will utilize directed acyclic graphs (DAGs) to determine the minimum necessary adjustment sets of confounders to control for within the comparative multivariable model. This approach mitigates the risk of bias that may arise from conditioning on intermediate covariates or colliders and mediators (Textor et al. 2011; Tonnies et al. 2022). The causal diagram for the comparative multivariable Cox model is complemented by a literature review and discussion to identify confounders, colliders, mediators and prognostic factors (Austin and Stuart 2015; Lederer et al. 2019). By adjusting the minimum sufficient adjustment sets of confounders in our comparative model, we will be able to block any backdoor bias paths (remove relevant confounding) when estimating the total causal effect of surgical treatment modality on all-cause mortality.

We will consider the following baseline characteristics (measured before or at time-zero) as potential confounders: Age at colon cancer diagnosis, sex, year of surgical treatment (classified according to the implementation and update series of the German S3- guideline for colorectal cancer (German Guideline Program in Oncology 2019) as 2008–2009 [pre-implementation], 2010–2014 [first update], or 2015–2018 [second update]), tumor laterality (right-sided [caecum and ascending colon] tumor or left-sided [descending and sigmoid colon] tumor), hospital type (classified as either a registered colorectal cancer center or other group), performance status (ECOG ≤ 2 or Karnofsky performance status score ≥ 50%), and histologic grade (low, intermediate or high), UICC stage (I, II or III), and local tumor size (T-stage). In addition, we will adjust the following two variables that serve as quality indicators of performed surgical procedure: minimum number of harvested lymph nodes (classified as < 21 or ≥ 21) (Choi et al. 2010), and local residual tumor status within 3 months of diagnosis (no (R0), yes (R1 + R2), not assessable or missing). We will also extract the following dates accurate to the month (date of birth, diagnosis, surgery, death, neo/adjuvant therapy initiation, and conversion to open surgery) and other covariates (project specific pseudonym, tumor IDs, cause of death).

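### Calendar time is adjusted only in three guideline bands of 2, 5 and 4 years, so the period-specific analyses state no calendar adjustment inside a band

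*Protocol article*

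**What the plan says.** The cohort is diagnosed "between January 1, 2008 and December 31, 2018", which is 11 calendar years. Calendar time appears in three places in the protocol article:

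- **Table 1, Covariate adjustments:** "treatment period (2008–2009, 2010–2014, 2015–2018" is listed among the clinical characteristics, and the emulated trial uses the same list.
- **Statistical analysis, potential confounders:** the variable is year of surgical treatment, "classified according to the implementation and update series of the German S3- guideline for colorectal cancer", with the bands given "as 2008–2009 [pre-implementation], 2010–2014 [first update], or 2015–2018 [second update".
- **Design of the target trial and the emulated trial:** "treatment period-specific analyses will be performed to mitigate potential bias that may be induced by changes in clinical knowledge and practice over time".

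No continuous or finer calendar term is named for the treatment weights, the censoring weights or the outcome model. Dates of diagnosis and surgery are to be extracted to the nearest month. The imputation model is to use all variables of the analysis dataset.

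**The concern.** The authors name change over time as a source of bias and list treatment period as a potential confounder. The stated remedy reaches only part of it. In the pooled analysis, a patient from January 2010 and one from December 2014 have the same value of the calendar covariate. In an analysis restricted to 2010–2014, that covariate is constant and drops out of the weight models, so the stated covariates give no calendar adjustment across five years.

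Two conditions would turn this into bias: use of laparoscopy changed within the band, and survival changed within the band for reasons other than surgical approach. If laparoscopy rose while mortality fell, laparoscopic patients would on average be diagnosed later than open patients, and part of the general gain in survival would be credited to the approach. Neither planned safeguard would reveal this. Bootstrap intervals describe sampling error, and the E-value analysis is aimed at BMI, comorbidity and previous abdominal surgery.

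The coding has a second, smaller weakness. The confounders are described as measured at or before time-zero, which Table 1 sets at diagnosis. Surgery may follow up to three months later, so year of surgery is not strictly known at time-zero. Date of diagnosis is.

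**Working it through.** The plan states no figure on this point to reproduce. The check asks how large the within-band bias could be.

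**Inputs from the article.** The bands are 2008–2009, 2010–2014 and 2015–2018, that is 2, 5 and 4 years. The widest holds 5/11 = 45% of the accrual years.

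**Assumptions (not in the article).** The true hazard ratio is 1. Accrual is even over 2010–2014. The laparoscopic share rises linearly, either from 20% to 40% or from 10% to 50%. The mortality hazard falls by d = 2% or 4% per year of diagnosis. No other covariate absorbs the trend.

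**Step 1: gap in mean diagnosis date.** Let t run from 0 to 5 years and let the share be p(t) = a + (b − a)t/5. Then

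mean t (laparoscopic) = ∫t·p dt / ∫p dt, and mean t (open) = ∫t·(1 − p) dt / ∫(1 − p) dt.

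In both scenarios ∫p dt = 5 × 0.30 = 1.5, ∫(1 − p) dt = 3.5 and ∫t dt = 12.5.

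- 20% to 40%: ∫t·p dt = 0.2 × 12.5 + 0.04 × 125/3 = 4.167. Laparoscopic mean = 4.167/1.5 = 2.78 years. Open mean = (12.5 − 4.167)/3.5 = 2.38 years. Gap = 0.40 years.
- 10% to 50%: ∫t·p dt = 0.1 × 12.5 + 0.08 × 125/3 = 4.583. Laparoscopic mean = 4.583/1.5 = 3.06 years. Open mean = (12.5 − 4.583)/3.5 = 2.26 years. Gap = 0.79 years.

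**Step 2: spurious hazard ratio**, approximately (1 − d)^gap.

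| Laparoscopic share | d = 2% | d = 4% |
|---|---|---|
| 20% to 40% | 0.98^0.397 = 0.992 | 0.96^0.397 = 0.984 |
| 10% to 50% | 0.98^0.794 = 0.984 | 0.96^0.794 = 0.968 |

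Computing events over person-time for 60 months with exponential survival and an assumed 5-year mortality of 28% gives the same four values to three decimals.

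**Step 3: milder assumptions.** With five yearly steps, a share rising from 20% to between 30% and 50%, and a hazard fall of 1–3% a year, the spurious hazard ratio is 0.980–0.997.

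**Step 4: the other bands.** The gap shrinks with the square of band width when the yearly rise and the mean share (30%) are unchanged. For 2015–2018 it is 0.25–0.51 years, giving hazard ratios of about 0.98–0.99. For 2008–2009 it is 0.06–0.13 years, giving 0.995–0.999. The issue matters mainly in the two wide bands.

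**The case against.** The bands have a stated reason: they follow the guideline versions, which suits an analysis of changing practice, and the article promises to mitigate bias, not remove it. Nothing here contradicts itself. The article is condensed, and a fuller model specification may exist. The bias is small under plausible assumptions, and the calculation ignores the other planned adjustments, such as age, stage, hospital type and performance status. The imputation model may already hold calendar date, because it takes all variables of the dataset and dates are extracted.

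Most of this stands, and it makes the point an improvement and not an error. It does not remove the point. The three-level coding is stated twice as the covariate, so it is a choice made in the text and not a detail left out. A good reason for reporting by guideline band is no reason to adjust by band alone.

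A reader might go further. The section on study setting dates "the nationwide implementation of clinical cancer registries, enacted by the Cancer Early Detection and Registry Act (Krebsfrüherkennungs- und -registergesetz, KFRG) in April 2013". That month falls inside the middle band, with 39 months before it and 21 from then on (21/60 = 35%). One might infer that the 2010–2014 results mix two data-capture regimes. The article does not support that inference. It gives the date a national law was enacted, not a date on which this registry changed its variables, coverage or follow-up. It describes "a registry providing ≥ 90% completeness of coverage" and reports no break. Any capture effect on the hazard ratio would need an invented step in recorded mortality, of unknown size and direction. A change in follow-up capture would also not divide patients neatly by diagnosis date. Patients diagnosed from January 2010 to March 2013 have on average (60 − 39/2)/60 = 67.5% of their potential 60-month follow-up after the law.

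**Conclusion.** The point holds as a modest weakness in adjustment. As stated, calendar time is controlled only between guideline bands, and the period-specific analyses have no calendar control within them. Under the assumed uptake and trend, the spurious hazard ratio in 2010–2014 is about 0.97–0.99, in favour of laparoscopy. The direction depends on uptake rising while mortality falls, and it reverses if only one of these does. If either was flat within a band, there is no bias from this source in that band. A 1–3% shift will seldom decide a conclusion alone, but it is systematic, the planned intervals would not show it, and it is easily avoided. The case rests on the wide bands, not on the 2013 law.

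**What to change.** Add calendar date of diagnosis as a continuous term to the treatment-weight and censoring-weight models, and state explicitly that it is in the imputation model. Do this in the pooled analysis and within each period-specific analysis. A restricted cubic spline suits the pooled analysis and the two wider bands; a linear term is enough for 2008–2009. Keep the three guideline bands for reporting results. Specify the term before the period-specific estimates are seen, so that it cannot look data-driven.

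As an optional descriptive check, report completeness of the key covariates by year of diagnosis. That would show whether capture changed around the 2013 law. No indicator for April 2013 is needed in the models.

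The cost is a few parameters in models already planned and slightly more variable weights, chiefly in the short first band. No new data are required, because the diagnosis month is already on the extraction list.

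### Lymph-node yield and residual tumour status result from the operation, so adjusting for them can bias the laparoscopic-versus-open effect in either direction

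*Protocol article*

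**What the plan says.** **Timing.** In Table 1 of the Protocol article, the follow-up row for the emulated trial reads: "Patients will be followed from time-zero (date of diagnosis) until death from any cause". The section on the design of the target trial and the emulated trial adds: "The initiation of treatment will have to occur within the first three months after the diagnosis of colon cancer (defined grace-period". Surgery therefore comes after time-zero.

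**Confounders.** The Statistical analysis section opens its covariate list with: "We will consider the following baseline characteristics (measured before or at time-zero) as potential confounders". The items are age, sex, treatment period, laterality, hospital type, performance status, grade, UICC stage and T-stage.

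**The two further variables.** The same paragraph continues: "In addition, we will adjust the following two variables that serve as quality indicators of performed surgical procedure: minimum number of harvested lymph nodes" (split at 21 nodes), and then "local residual tumor status within 3 months of diagnosis (no (R0), yes (R1 + R2), not assessable or missing". In the target-trial column of Table 1, the covariate-adjustment row includes "local residual tumor margin status (yes, no, or not assessable" and the node count. The emulated-trial column refers back to that list unchanged.

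**Estimand.** The research question asks whether laparoscopic colectomy improves 5-year overall survival compared with open colectomy. The causal contrast for the emulation is the observational analogue of the per-protocol effect of the two operations within the first three months. No controlled or natural direct effect is mentioned.

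**Comparator.** The Cox comparator described under Sensitivity and comparator analyses uses a DAG-derived set of age, grade, performance status and laterality. It contains neither of the two variables.

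**The concern.** How many nodes are harvested and whether the margin is clear become known only once the operation is done. By the plan's own description they reflect how well it was done. If the approach influences either one, and either one influences survival, part of the approach's effect runs through them. A patient or surgeon choosing between the operations wants that part counted. Holding it fixed answers a different question: how the two approaches would compare if resection quality were the same.

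Conditioning on a post-operative variable can also open a non-causal path where an unmeasured factor affects both that variable and survival. The article concedes that BMI, comorbidity and earlier non-malignant abdominal surgery are not recorded, so such factors are plausible.

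At stake is the meaning of every main result: the hazard ratio, the absolute risk differences and the differences in restricted mean survival time.

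**Working it through.** The article gives no sample size, event count, effect size, or node or margin distribution by arm. There is no planned figure to reproduce. The check is one of time order, followed by an illustration on assumed inputs.

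**1. Time order**

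| Step | When | Source in the Protocol article |
|---|---|---|
| Time-zero | Date of diagnosis | Table 1, Follow-up |
| Operation | Up to three months later | Table 1, Grace-period; design section |
| Node count, residual tumour status | At or after the operation | Statistical analysis, which calls them indicators of the quality of the performed procedure |
| Outcome | Death up to 60 months | Table 1, Outcome |

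Both variables lie between treatment and outcome. Table 1 also lists them for the hypothetical randomised trial, where confounding cannot be the reason for adjusting.

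**2. Where they might enter**

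The article does not say which model receives them.

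- *Outcome model:* the treatment coefficient becomes conditional on resection quality.
- *Treatment weights:* the arms are made alike on a consequence of treatment.
- *Censoring weights:* a clone leaves the open arm because laparoscopy was done. Its node count and margin come from that same laparoscopic operation, so the weight would use information produced by the event that triggers censoring. Before surgery neither variable exists.
- *Balance check:* the plan accepts absolute standardised differences up to 10%. For proportions p1 and p0 the difference is |p1 − p0| / √{[p1(1 − p1) + p0(1 − p0)]/2}. With assumed R1/R2 rates of 3% and 6% this is 0.03/√[(0.0291 + 0.0564)/2] = 0.145. With assumed rates of 40% and 50% for at least 21 nodes it is 0.10/√[(0.24 + 0.25)/2] = 0.202. Both exceed 0.10, so a real difference in surgical quality would be read as imbalance.

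The last three items hold only if the variables are in the weight models or the set checked for balance.

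**3. Approximate size of each mediated component (all inputs assumed)**

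Component = [1 + p_lap(HR − 1)] / [1 + p_open(HR − 1)].

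- Margins, 3% laparoscopic vs 6% open: HR 2 gives 1.03/1.06 = 0.972; HR 3 gives 1.06/1.12 = 0.946.
- Nodes ≥21, 40% laparoscopic vs 50% open: HR 0.7 gives 0.88/0.85 = 1.035; HR 0.8 gives 0.92/0.90 = 1.022.

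In this example the two components oppose each other. Their products run from 0.946 × 1.022 = 0.967 to 0.972 × 1.035 = 1.006, a net shift of about 3% at most.

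**4. Exact calculation for other assumed patterns**

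Set-up: equal arms, no confounding, exponential survival with reference hazard 0.05 per year for 5 years, and two binary mediators that are independent within arm. HR for R1/R2 is 2.5. HR for ≥21 nodes is 0.8 (0.75 in row 3). The direct HR is 0.90 (1.00 in row 3). Risk in a cell = 1 − exp(−5 × 0.05 × direct HR × node HR × margin HR). The total effect averages cell risks over each arm's own mediator distribution. The adjusted effect averages over the pooled distribution. HR is ln(1 − risk_lap)/ln(1 − risk_open).

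| Row | ≥21 nodes, lap/open | R1/R2, lap/open | Total HR (5-year risk difference) | Adjusted HR (5-year risk difference) | Share of log HR removed |
|---|---|---|---|---|---|
| 1 | 50/50% | 3/3% | 0.901 (−1.9 points) | 0.901 (−1.9) | 0% |
| 2 | 55/45% | 2/4% | 0.859 (−2.7) | 0.901 (−1.9) | 31% |
| 3 | 60/40% | 2/5% | 0.910 (−1.7) | 1.000 (0.0) | 100% |
| 4 | 45/55% | 4/2% | 0.944 (−1.0) | 0.901 (−1.9) | −81% (benefit overstated) |

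Leaving both variables out returns the total effect in every row, by construction. Bias from unmeasured common causes is not included.

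**The case against.** **Self-contradiction.** A reader might infer that the plan breaks its own rule, because the paragraph on DAGs says "This approach mitigates the risk of bias that may arise from conditioning on intermediate covariates or colliders and mediators" and speaks of blocking bias paths "when estimating the total causal effect of surgical treatment modality on all-cause mortality". Both statements are about the comparator Cox model, and its adjustment set leaves out node count and residual status, so that model keeps to the rule. Likewise, the requirement to be measured by time-zero is attached to the confounder list, and the two quality indicators are added to that list as a separate item. No literal contradiction can be claimed, and the research question does not use the words total effect. That the per-protocol contrast includes effects through resection quality is an inference: the contrast compares operations, and nothing in the article sets resection quality aside.

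**Model not named.** The weights are described as depending on confounding factors, and the two variables might be meant for the outcome model only. This makes the censoring-weight and balance arguments conditional. It does not rescue the adjustment, which is misplaced in any of the three models.

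**Size.** Every numerical input above is assumed. If approach affects neither variable, mediation bias is zero. The tempting stronger statement, that adjustment necessarily removes part of the effect, is not supported: row 4 shows the opposite.

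**Proxy for hospital quality.** Node yield may partly reflect the institution. Hospital type and treating institution are already among the Table 1 covariates, so a post-operative measure is not needed for that purpose.

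**Conclusion.** The point holds. The article commits to adjusting the emulated analysis for two consequences of the operation without defining an estimand that would call for it. The result can be biased towards or away from the null. The amount cannot be calculated from the article, and it is zero if approach affects neither variable. The illustrations show only that ordinary-looking differences between arms could matter; they do not predict the bias in this registry.

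There is a secondary consequence. The comparison with the DAG-guided Cox model is meant to show what the emulation changes. The two analyses already differ in more than one way, and if only the emulated one adjusts for post-operative variables, a difference is harder still to attribute to the emulation.

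The conclusion rests on two premises: node yield and margin status arise from the operation, which the article says, and the contrast of interest is between the operations as performed, which is the natural reading of its per-protocol definition.

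**What to change.** - Remove harvested node count and residual tumour status from the main-analysis adjustment set, meaning the treatment-weight, censoring-weight and outcome models.
- Remove both from the covariates checked against the 10% balance limit.
- Delete both from the covariate-adjustment row of Table 1 for the target trial and for the emulated trial.
- Report both by arm as descriptive results on surgical quality. If the effect net of resection quality is of interest, put it in a separately labelled mediation analysis with its own direct-effect estimand and assumptions.

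This changes wording and model specification only. No additional data are needed, and both variables can still be extracted for reporting.
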